**Fig. 3 Fig3:**
[figure not shown]
The adapted ERIC procedure

To begin the modified ERIC process from an evidence-based foundation, we plan to use the results and recommendations from a recent systematic synthesis of 44 published reviews on eHealth implementation [46], focused on EHR, CDS, and PPM tools in primary care (Fig. 4). The strategy selection and incorporation process are described in detail in Additional file 1. Briefly, the development of the PPM tool for pediatric HTN will follow co-design workshops (Aim 1) explicitly focusing on these aspects. Strategies 2 and 3 are already in place and facilitated by AllianceChicago’s shared health information technology infrastructure. Strategies 4–7 will be the focus of the ERIC process for optimization. Concerning Strategy 4, we have designed our study activities to prospectively involve stakeholders and champions in the design of the tool and the initial implementation strategy package. Planning (Strategy 5) is also built into the study design and the process of developing and optimizing the implementation strategy and can also be modified with each successive cluster rollout. For training and education (Strategy 6), numerous discrete implementation strategies exist which offer significant adaptability for the needs of the intervention [65]. Finally, for Strategy 7, we will follow best practices for audit and feedback [66–68]. We will use established guidelines [69–71] to ensure accurate and detailed specification of the strategies used within the package as part of the mixed methods analytic plan.

**Fig. 4 Fig4:**
[figure not shown]
Recommendations for the implementation of eHealth innovations

Beyond Ross et al.’s summary, we anticipate using strategies unique to a PPM tool. The primary functionality of a PPM tool that distinguishes it from CDS and other eHealth interventions is the ability to examine cohorts of the clinic population for “missed opportunities” in guideline adherence. This population-based snapshot, as opposed to a single patient (i.e., point-of-care) perspective, allows clinic staff to examine recent and upcoming patient visits, as well as patients inactive in care, for indicators of need for outreach to re-engage in care for attention to HTN-related concerns. The precise manner in which these unique aspects of the PPM tool will be used in this study are unknown given the dearth of such tools for children.

The adapted ERIC process of barrier assessment, strategy selection, and optimization will be further organized through the use of the Implementation Research Logic Model [72, 73] as a process evaluation tool to depict iterative changes over time, and causal pathway diagrams [74]. Both of these methods specify the associations between identified barriers, specific implementation strategies, the mechanism(s) by which the strategy addresses the barrier, and the desired outcomes.

### Assessment strategy, measures, and data analysis

The proposed study incorporates surveys and stakeholder interviews/meetings with multiple respondents (e.g., providers, key stakeholders). Mixed methods approaches for implementation research [75–77] are central to evaluating the tailoring and optimization of the PPM and CDS tools (Aim 1) and the implementation strategy package (Aim 2).

#### Aim 1: Tailor CDS and optimize PPM tools that addresses multilevel implementation barriers

The co-design workshops (*n* = 2) and stakeholder panel meetings (*n* = 2 meetings), and the “think aloud” portion of usability testing sessions (*n* = 20 total), will be evaluated through a sequential mixed methods approach involving rapid qualitative analysis of video recordings alongside quantitative results of the System Usability Scale [64]. In this project, the CFIR [56] interview guide will be used to semi-structure the stakeholder panel meetings. To ensure that qualitative results can be processed within our timeframe, we use a quick and comprehensive qualitative analysis strategy called Framework-Guided Rapid Analysis [78] in which a structured template based on the CFIR [56] analysis template is generated. To further reduce the necessary time for qualitative data processing, we will (1) identify themes and conduct content analysis directly from audio recordings, which can be done without the need for time-consuming transcription [79], and (2) provide “summary templates” rather than the typically lengthy results from intensive coding. Implementation researchers have used this method successfully when quick turn-around is required [80]. These qualitative analysis methods have been found to be reliable while requiring only about 13% more time than the recording [79], and some have found that a rapid approach is comparable to thematic analysis in terms of identifying key actionable findings [81]. Use of the CFIR interview guide and analysis template ensure that aspects of the domains and subdomains mentioned by the panel are captured, and uniform terminology and the definitions of other implementation researchers are used, which will increase rigor and reproducibility.

All qualitative data processing and analysis will be done by a trained Research Associate and a Research Assistant, overseen by JS. For reliability, 20% of panel meetings and “think aloud” tasks will be double-coded in order to calculate reliability [82]. Disagreements in coding will be resolved via expert consensus among the investigative team led by JS, who has led studies using qualitative and mixed methods [83–85] and rapid qualitative analysis methods and the CFIR tools. The mixed methods analytic approach in this aim will be a “merge the data” approach described by Palinkas and Cooper [75], which involves bringing together quantitative and qualitative data through complementarity [76, 77].

#### Aim 2: Develop an implementation strategy package

Evaluation of the strategy development will be mixed methods involving qualitative data analysis from key informant interviews and the stakeholder panel meetings and the results of quantitative surveys.

#### Qualitative analysis of the optimization process

Procedures for the collection, rapid analysis, and reliability of qualitative data are described in Aim 1. To ensure detailed reporting of the implementation strategy package, we will follow published guidelines [69] and use the Implementation Research Logic Model [72, 73]. This is critical for interpretation and rigor and reproducibility of the study, as well as costing of these activities (see “Cost analysis” section below).

#### Quantitative analysis of the development process

Surveys administered during development activities of this project focus on usability of the tool (see Aim 1) and the feasibility, appropriateness, and acceptability of the tool and its implementation strategy package assessed via brief, validated surveys developed by Weiner et al. [86] after tool and strategy package development.

#### Mixed methods analysis

The mixed methods analytic approach is sequential (“Connect the dots”) [76, 77] for integrating the qualitative data with the quantitative data. This approach will provide a detailed evaluation of the development process and the specific strategies involved in the package.

#### Cost analysis

Economic analyses are central to the implementation evaluation and for providing data of use to potential adopters (e.g., administrators, policy makers). Our cost evaluation within this project will focus on estimating the costs associated with implementing each discrete strategy and the package of strategies developed by the stakeholder panel. This cost analysis will be conducted from the perspective of a provider organization that may wish to adopt the multicomponent strategy developed in this study. An ingredient-based cost analysis procedure, including costs for tool refinement and optimization and integrating it with the EHR, training providers and other stakeholders, time of provider usage, and other personnel time to support implementation, will be employed to estimate costs associated with each discrete strategy. Strategy costs will be aggregated to estimate total package costs. Consistent with the aims of this project, we will estimate total cost of implementation preparation activities (that is, the activities required to get ready for implementation prior to any patient benefit) as has been done in prior implementation studies led by NJ and JS [87, 88]. Using an activity-based costing approach will allow us to value activities both locally (Chicago, Illinois) and from national data sources (e.g., Current Population Survey, US Department of Labor), providing estimates relevant for scale up in new pediatric care settings nationwide.

#### Normalization

Defined as the perception of *potential* standardization of the PPM and CDS tools, normalization will be assessed using the NoMAD instrument [89, 90]. The NoMAD assesses staff perceptions of factors relevant to embedding health information technology that changes typical work practices. Based on Normalization Process Theory [91], the 23-item NoMAD is concerned with: *implementation* (bringing a practice or practices into action), *embedding* (when a practice or practices may be routinely incorporated into everyday work), and *integration* (when a practice or practices are reproduced and sustained in the social matrices of an organization) [89]. The NoMAD is particularly relevant for evaluating practice changes in primary care involving health information technology interventions [92–94]. It will be administered to all involved stakeholders (physicians/providers/practice leaders) in M11.

### Protocol modifications and current status

Based on feedback from our scientific advisory board, we have made three modifications to the protocol. First, to provide contemporary baseline adherence rates to the guidelines prior to implementation, we will perform two secondary data analyses of EHR data from the AllianceChicago network of CHCs to characterize the prevalence of correct diagnosis of pediatric HTN and elevated BP. These analyses will be conducted on two time periods. The first will be 1 year prior to the guideline changes (visits occurring between December 2016 and December 2017), and the second period will be the 2 years after the guidelines changed and minimal EHR capacities were added (e.g., automatic calculation of age-specific percentiles). Second, consistent with the goal of Aim 1 (to refine a PPM tool that addresses multilevel implementation barriers), we will invite pediatric patients at risk for HTN and their caregiver(s) to participate in a brief interview to better understand their needs and perspectives around the assessment, diagnosis, and management of pediatric HTN to inform implementation strategies concerning raising awareness and motivating adherence with guideline-based care, such as returning for a repeat BP measurement after a first elevated BP. Third, also aligned with Aim 1, pediatric primary care providers will be invited to complete an online survey to better understand their perspectives around identifying and managing pediatric HTN. Feedback from the patient-caregiver interviews and provider surveys will help us better design and implement the PPM tool and associated implementation strategies to support guideline-adherent care for HTN.

At submission of this protocol, the project is well underway. Specifically, we have recruited the stakeholder panel and the meeting dates have been scheduled; developed and pilot-tested the provider survey; and convened a meeting of the Scientific Advisory Board. Further, the first set of secondary data analyses of EHR data have been conducted and a manuscript is currently being prepared for submission.

It is worth mentioning that we are currently in the middle of the COVID-19 pandemic in the state of Illinois, which includes a stay-at-home order. AllianceChicago CHCs, like most healthcare systems across the nation, are shifting their focus to managing the pandemic. Accordingly, we have temporarily suspended administration of the provider survey and will hold meetings of the stakeholder panels virtually. Our team will continue to modify the protocol as required to meet the shifting needs of our stakeholders and collaborators in the healthcare system during this pandemic, while also adhering to public health guidelines, guidance from Northwestern University, and recommendations from the Center for Disease Control and Prevention and the Illinois and Chicago Departments of Public Health.

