## Background

Target organ damage, especially left ventricular hypertrophy associated with heightened risk for cardiovascular events in adults, is detectable in youth with primary hypertension (HTN) [1, 2]. Risk factors for adult HTN and concomitant target organ damage from HTN have been shown to begin in childhood [3–5]. Hypertensive children are more likely to have adult hypertension and metabolic syndrome [5, 6]. Primary prevention is critical given estimates that almost 10% of HTN in adults could be prevented if high blood pressures (BP) in childhood were recognized and treated [7–10]. The need to diagnose and manage HTN is further magnified due to increasing rates of childhood obesity [11–13] that indicate disproportionate effects on those who are disadvantaged economically and socially [14–16]. Guidelines for pediatric HTN were issued by the American Academy of Pediatrics (AAP) in 2017 [17] yet the diagnosis of pediatric HTN is often missed, and management may not follow the guidelines due to the complexity of interpreting youth BP standards, diagnosing HTN, and variable familiarity with managing pediatric HTN among pediatric healthcare providers [18].

A recent study in community health centers in the Chicago area found only 6.1% among 1478 children (age ≥ 3 and < 18 years) who met criteria for abnormal BP—based on BP values from clinical encounters recorded in the electronic health record (EHR)—were correctly diagnosed [19]. Evidence suggests that wide adherence to the HTN guidelines would result in lower risk for target organ damage to the heart and the kidneys and HTN-related cardiovascular disease in adulthood [17]. There is a pressing need for effective implementation strategies to ensure adherence to the pediatric HTN guidelines in primary healthcare systems, particularly those that serve high rates of children and adolescents at greatest risk for HTN due to the health disparities associated with obesity and or low birth weight [20–22].

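### The EHR window labelled as the year before the guideline change covers nearly all of 2017, the year of issue, so it is pre-guideline only if issue fell in December 2017

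*Protocol article*

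**What the plan says.** The section *Protocol modifications and current status* adds secondary analyses of EHR data from the health-center network. Their purpose is "to provide contemporary baseline adherence rates to the guidelines prior to implementation", and the quantity estimated is the prevalence of correct diagnosis of pediatric hypertension and elevated blood pressure. "These analyses will be conducted on two time periods":

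- First period: "The first will be 1 year prior to the guideline changes (visits occurring between December 2016 and December 2017".
- Second period: "the second period will be the 2 years after the guidelines changed and minimal EHR capacities were added". The example given of an added capacity is automatic calculation of age-specific percentiles. No calendar dates are given.

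The only dating of the guideline elsewhere is to the year. The *Background* says: "Guidelines for pediatric HTN were issued by the American Academy of Pediatrics (AAP) in 2017". No month or day appears in the article. The modifications section also reports that a first set of the EHR analyses has been run and that a manuscript is being prepared.

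**The concern.** A period described as lying before a guideline should end before the guideline appears. This one runs into December of the year in which the guideline was issued. Unless issue came at the very end of that year, the period mixes visits made before and after it.

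The label matters because the outcome depends on the guideline. The section on the challenges of the 2017 guidelines lists the change of terminology to elevated blood pressure among the difficulties, so what counts as a correct diagnosis may differ by guideline version. A window that straddles the issue date gives a rate belonging to neither version. The rate is meant as a baseline ahead of implementation, and the tools are to be tested with patients in a subsequent study, so a mislabelled figure could be carried forward.

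The start of the second period is also open. It is placed after the guideline change and after the EHR additions. If these fell on different dates, December 2017 may be the EHR date, which would explain a window that covers the year of issue. The article does not say.

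**Working it through.** **Inputs.** First window, December 2016 to December 2017, and its label of 1 year (*Protocol modifications and current status*). Guideline issue in 2017, month not given (*Background*). The days of the month on which the window opens and closes are not given, so four readings are tried. The issue date is an assumption, varied across 2017.

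**Formulas**, counting both end days:

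- Window length L = end − start + 1.
- Post-issue days O = max(0, end − issue + 1).
- Post-issue share f = O / L.

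**Step 1: the plan's own figure.** From 1 December 2016 to 1 December 2017, L = 366 days, or 12.0 months. From 31 December to 31 December, L is also 366. The stated 1 year is reproduced. The two outer readings give 336 days (11.0 months) and 396 days (13.0 months).

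**Step 2: share of the window after issue.**

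| Assumed issue date | 1 Dec 2016 to 1 Dec 2017 (L = 366) | 1 Dec 2016 to 31 Dec 2017 (L = 396) | 31 Dec 2016 to 31 Dec 2017 (L = 366) | 31 Dec 2016 to 1 Dec 2017 (L = 336) |
|---|---|---|---|---|
| 1 Jan 2017 | 335 d, 91.5% | 365 d, 92.2% | 365 d, 99.7% | 335 d, 99.7% |
| 1 Apr 2017 | 245 d, 66.9% | 275 d, 69.4% | 275 d, 75.1% | 245 d, 72.9% |
| 1 Jul 2017 | 154 d, 42.1% | 184 d, 46.5% | 184 d, 50.3% | 154 d, 45.8% |
| 1 Oct 2017 | 62 d, 16.9% | 92 d, 23.2% | 92 d, 25.1% | 62 d, 18.5% |
| 1 Nov 2017 | 31 d, 8.5% | 61 d, 15.4% | 61 d, 16.7% | 31 d, 9.2% |
| 1 Dec 2017 | 1 d, 0.3% | 31 d, 7.8% | 31 d, 8.5% | 1 d, 0.3% |
| 31 Dec 2017 | 0 d, 0% | 1 d, 0.3% | 1 d, 0.3% | 0 d, 0% |

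Issue on or before 1 November gives an overlap of at least 8.5% on every reading. The overlap then shrinks through November: issue on 30 November with a window closing on 1 December leaves 2 days, 2/366 = 0.5%.

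**Step 3: when the label is exactly right.** If the window closes on 1 December 2017, an issue date from 2 to 31 December gives no overlap. That is 30 of the 365 dates in 2017. If it closes on 31 December, no date in 2017 gives zero overlap, though the last day leaves only one day.

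**Step 4: effect on the rate.** Let p0 be the rate of correct diagnosis before issue and p1 the rate after. With visits spread evenly in time, the first-period rate is (1 − f)·p0 + f·p1. If p1 applies at once and stays constant, the second period minus the first is p1 − [(1 − f)·p0 + f·p1] = (1 − f)·(p1 − p0). The difference is therefore reduced by the fraction f: by 42-50% for issue on 1 July and by 17-25% for 1 October. If practice changes slowly, the loss is smaller than f.

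**The case against.** The strongest answer is that the passages do not contradict each other. Read literally, the modifications section places the change at about December 2017, and that is in 2017. A reader might infer that post-guideline visits have definitely been counted as pre-guideline. The article does not support that, because it gives no issue month. The point has to stay conditional.

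The analysis is also descriptive. It characterizes prevalence in two periods and states no test, no effect estimate and no attribution of a difference to the guideline or the EHR feature. A reader might infer that a planned pre/post inference is biased, or that the two causes are confounded in it, but no such inference is planned. The joint anchor of the second period is stated openly. Dilution arises only if the two rates are set against each other. Its full size assumes immediate uptake, which sits poorly with the article's own account of weak adherence.

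Two further inferences fail. December to December is ordinarily 12 months, so the window is not shown to be 13 months long. Nor is the stated aim of a contemporary adherence baseline defeated by the early window, since the second period can supply it.

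Finally, exact dates might be left to the EHR manuscript. That excuses some missing detail. It does not excuse a stated window and a stated label that agree only if issue fell in one particular month.

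**Conclusion.** The concern holds in conditional form. The first window takes in all of January to November 2017 on any reading, and the guideline is dated only to 2017. Any issue date in those eleven months makes the period mixed. A December issue leaves between none and 31 days of overlap (0-8.5%).

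No single size can be given. The range rests on an assumed issue date and on visits spread evenly over the window; carrying it over to a difference between periods also requires immediate and lasting change in practice. The second period cannot be placed on the calendar from the text.

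It is a should-fix. A reported rate may carry the wrong label, but no sample size, decision rule or hypothesis depends on it. Aims 1 and 2 rest on design work, usability testing, surveys, interviews and costing.

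**What to change.** - State the actual guideline issue date. End the first window on the last day before it and take the 12 months up to that day.
- If December 2017 is in fact the date of the EHR change, relabel the period as before the EHR change, and report visits before and after guideline issue separately within it.
- Give calendar start and end dates for the second period, and the dates of both events that anchor it.
- Apply this to the analysis already run before the manuscript is submitted. If issue was in December 2017, stating the date and closing the window on the day before is enough.

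The cost is a date filter and a re-run, and possibly a few earlier months of EHR data if the first window has to move back. No change to Aims 1 and 2 is needed.

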## Discussion

The ultimate goal of the proposed project is to develop a feasible implementation strategy package to increase adherence to clinical practice guidelines for pediatric HTN diagnosis and management. We will accomplish this aim using a PPM tool and CDS at the point of care. This will broaden the reach of HTN diagnosis and management by providing a tool that assists providers and benefits an entire patient population.

The protocol will extend the existing literature in two novel ways. First, we will design and implement a PPM tool to support the adoption of AAP guidelines for the diagnosis and treatment of pediatric HTN. No such sophisticated, EHR-integrated tool currently exists for pediatric HTN, despite evidence that PPM tools are effective at improving diagnosis and management of multiple chronic health conditions (including HTN in adults), and PPM tools are unique and underutilized tools for guideline implementation in pediatrics. Additionally, while the majority of existing PPM tools are for adults, this innovation will focus on children and adolescents. Second, we will leverage an innovative stakeholder-driven process for tool development using UCD methods and development of an implementation strategy package based on best available evidence from the field of implementation science and a low-cost adaptation of the ERIC process. Third, we will conduct a prospective implementation cost evaluation informed by stakeholders to ensure that critical questions informing economic sustainability and incremental cost-benefits are answered. Inadequate cost evaluation is a top reason for failure to implement [95], and an insufficient proportion of implementation research studies include prospective economic evaluation [96]. Cost information is highly informative for potential adopter organizations and can be used to quanitify the monetary investment required to achieve adoption and the related clinical outcomes of interest.

We anticipate two specific challenges while conducting this study. First, the HTN guidelines currently require repeated measurement of pediatric patients 'BP. As discussed, this guideline receives low adherence among pediatric healthcare professionals who are managing large workloads and competing priorities. Further, it places a large burden on families to attend multiple medical appointments. The activities in Aim 2 will actively address this challenge through understanding the barriers specific to providers and families around this aspect of the AAP pediatric HTN guidelines. Second, accurate assessment of BP in pediatric patients is critical. This speaks to the need of accessible training for pediatric healthcare providers and availability of correct BP assessment tools. Incorporating training in simply measuring BP accurately for younger children (ages 2 to 5 years) and helping pediatric clinics obtain arm cuffs that are properly sized for youth with obesity might become necessary.

Identifying youth with HTN is the gateway to getting them into effective treatments that can prevent the deleterious progression of cardiovascular disease risk. Should the implementation strategy package for PPM tool adoption and guideline adherence be successful for pediatric HTN, findings will be translatable to other settings and for PPM of other chronic heart, lung, blood, and sleep conditions among children and adults, thereby decreasing the health care burden of target organ damage in the cardiovascular system, and other complications, in the adult years and improving overall population health.

